### Data collection

The demographic characteristics questionnaire will be developed in two sections. The first part is related to personal information, such as age, level of education, and occupational and economic status of couples. The second part is related to the history of pregnancy, such as the date of the last menstruation period, the expected date of delivery, and the recent pregnancy status.

The brief version of PES was first developed by DiPietro (2008) with 20 items. The first and second 10 items assess the uplifts and hassles among pregnant women. The items are scored based on a 4-point Likert scale ranging from not at all (0) to somewhat (1), quite a bit (2), and a great deal (3). The total scores for each section are within the range of 0-30, and the higher scores indicate higher levels of uplifts and hassles. The reliability of the tool has been measured with internal consistency of 0.82 and 0.83 for uplifts and hassles, respectively using Cronbach’s alpha [19]. In Iran, the Persian translation of this tool was carried out by Hajifoghaha, while its psychometric properties were determined by Ebadi. The face, content, and construct validity of PES have also been confirmed. In order to determine the reliability of the test, an internal consistency with a Cronbach alpha of 0.777 and 0.672 was used for uplifts and hassles, respectively. The intra-class correlation coefficients of 0.712 and 0.672 have also been used for uplifts and hassles, respectively. This tool is valid during 15-38 gestational weeks [26].

The WDEQ-A was developed by Wijma (1998) and consists of 33 items which are scored based on a 6-point Likert scale ranging from “not at all…” to “extremely…” The total scores obtained are within the range of 0-165, so that the scores of ≤ 37, 38-65, 66-84, and ≥ 85 are recognized as mild, moderate, severe, and clinical fear, respectively [27]. Notably, reverse scoring is applied to items 2, 3, 6, 7, 8, 11, 12, 15, 19, 20, 24, 25, 27, and 31. The reliability of the results during the last trimester has been estimated at 0.89 by Cronbach’s alpha, and the split-half reliability of the test has been obtained at 0.91 [20]. The Persian version of this questionnaire was developed by Abedi et al. in Iran, and the reliability of this scale has been reported at 0.64 for the whole pregnancy period using Cronbach’s alpha [26].

### Analytic plan

Feasibility of recruitment will be achieved if ≥ 30% of eligible participants enroll in the study, and ≥ 80% participants complete follow-up assessments at 36-38 weeks (PES, WDEQ-A, and birth preference) (T2); the first few days of postpartum (type of delivery) (T3). Feasibility of intervention adherence will be achieved if average proportion of intervention adherence rate is ≥ 0.8 (participating in six sessions from eight at least for both the virtual and in-person childbirth preparation training groups).

The collected data will be analyzed in the SPSS software (version 19) using descriptive statistics, such as frequency distribution tables. Also, the Chi-square test and one-way analysis of variance (ANOVA) will be used to compare the quantitative and qualitative variables in three groups, respectively. In addition, the paired *t* test will be employed for intragroup comparison. The *p* value of less than 0.05 will be considered statistically significant.

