### Measurements and feasibility outcomes

The primary outcome of the present study would be the study feasibility that will be assessed based on recruitment and intervention adherence for all of the participants in both groups.

The secondary outcome of the present study would be the improvement of pregnancy experience measured by the brief version of the pregnancy experience scale (PES) [19]. The secondary outcome would be the decreased FOC measured by the version A of Wijma Delivery expectancy/experience questionnaire (WDEQ-A) [20]. In addition, the other outcomes would be the birth preference and type of delivery, respectively. Data collection is shown in the flow diagram (Fig. 1). Data will be collected at 3 times by self-reporting method through Telegram messages: Recruitment (demographic characteristics questionnaire, PES, WDEQ-A) ≈ 18-20 weeks (T1); 36-38 weeks (PES, WDEQ-A, and birth preference) (T2); the first few days of postpartum (type of delivery) (T3).

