### Sample size

A useful introduction to feasibility and pilot studies is given by Sim and Lewis, who recommend at least 50 participants. Therefore, according to strong evidence, sample size 50 is considered in current study [21–23].

To determine the sample size for other variables in the present study, the sample size has been calculated with a test power of 80% and a significance level of 0.05. Moreover, it is considered that in-person and social media-based education could affect the type of delivery among the study groups, leading to a 25% decrease in cesarean sections, compared to the control group. By using the effect size equation and considering 10% sample drop, the total sample size has been estimated at 55 participants per group. It should be noted that the ratio of primiparous women undergoing a cesarean section in Iran is assumed to be 0.55 [24] based on the statistics, so the sample size is large enough to measure all variables in this study.$$n=\frac{{\left({z}_{1-\alpha\left/ 2\right.}\sqrt{2\overline{p}}\overline{q}+{z}_{1-\beta}\sqrt{p_1{q}_1+{p}_2{q}_2}\right)}^2}{{\left({p}_1-{p}_2\right)}^2}=\frac{{\left[\left(1.96\times \sqrt{2\times 0.42\times 0.57}\right)+\left(0.84\times \sqrt{\left(0.55\times 0.45\right)+\left(0.3\times 0.7\right)}\right)\right]}^2}{{\left(0.55-0.3\right)}^2}=50$$$$\overline{p}=\frac{p_1+{p}_2}{2}$$

The sample size for the other variable of the study (fear of childbirth) was determined to be 43 participants with the confidence level of 95%, the power test of 80%, and based on the Toohil et al. study standard deviation for intervention and control group was 13.1 and 9.7, respectively with *d* = 7 [25], which was less than the sample size calculated based on the type of delivery. The sample size for the other two variables (childbirth experience and birth preference) was less than the one calculated for the above variables.$$n=\frac{{\left({z}_{1-\alpha\left/2\right.}+{z}_{1-\beta}\right)}^2\times \left({s}_1^2+{s}_2^2\right)}{d^2}$$$$n=\frac{{\left(1.96+0.84\right)}^2\times \left({9.7}^2+{13.1}^2\right)}{7^2}\approx 43$$

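### The only between-group test sentence reverses chi-square and ANOVA, contradicting the plan's own sample-size section; the secondary between-group comparisons are affected, feasibility is not

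*Protocol article*

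**What the plan says.** The Analytic plan gives one rule for comparing the three groups: "Also, the Chi-square test and one-way analysis of variance (ANOVA) will be used to compare the quantitative and qualitative variables in three groups, respectively". For change within a group it names the paired t test ("test will be employed for intragroup comparison"), and it sets the significance level ("value of less than 0.05 will be considered statistically significant").

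The outcomes to which the rule applies are defined elsewhere in Methods:

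- **PES**, two subscales, uplifts and hassles: "The total scores for each section are within the range of 0-30" (Data collection).
- **WDEQ-A**: "The total scores obtained are within the range of 0-165" (Data collection).
- **The remaining two outcomes**: "the other outcomes would be the birth preference and type of delivery, respectively" (Measurements and feasibility outcomes).

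The Sample size section handles fear of childbirth with a two-means formula ("standard deviation for intervention and control group was 13.1 and 9.7, respectively with" d = 7). It handles type of delivery with a two-proportions formula, 0.55 against 0.30.

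**The concern.** The sentence pairs two lists in order. Chi-square is matched to quantitative variables and one-way ANOVA to qualitative ones, which is the reverse of what each test is for.

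This is the only between-group test rule in the article. The paired t test looks within one group at a time, so it cannot stand in for a comparison of virtual training, in-person training and control, which is what the secondary objective asks for.

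Followed literally, the rule would cross-tabulate a score running from 0 to 165 against group. That ignores the order of the values and gives no difference in means. The reported test would also not match the quantities for which the trial was sized. This is not detail left to a fuller document: the article states the rule and states it wrongly.

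**Working it through.** **1. Literal rule against outcome type**

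| Outcome | Type in the article | Test as written | Basis in Sample size section |
|---|---|---|---|
| PES uplifts, PES hassles | score, 0–30 each | chi-square | no calculation shown |
| WDEQ-A | score, 0–165 | chi-square | difference in means |
| Type of delivery | category | ANOVA | difference in proportions |
| Birth preference | category (levels not given) | ANOVA | no calculation shown |

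All four secondary outcomes get the wrong test. For the two with a printed calculation, the assigned test conflicts with that calculation. The primary outcome is judged by thresholds (at least 30% enrolment, at least 80% follow-up, adherence of at least 0.8) with no test, so it is outside the sentence.

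**2. The plan's own figure for fear of childbirth**

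n = (1.96 + 0.84)² × (9.7² + 13.1²) / 7² = 7.84 × (94.09 + 171.61) / 49 = 42.5, rounded up to 43. The stated 43 reproduces, which confirms that the plan regards WDEQ-A as a mean.

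**3. Chi-square on raw WDEQ-A totals**

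Inputs from the article: three groups, 50 per group before the allowance for drop-out, d = 7, SDs 9.7 (control) and 13.1 (intervention). Assumed: normal scores rounded to whole numbers, means 66 in control and 59 in both study groups, and SD 13.1 in both study groups. Results over 2,000 simulated trials:

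- About 49 distinct scores occur per trial, so the average expected count is 50 / 49 ≈ 1 per cell.
- Essentially all expected counts are below 5, about 65% are 1 or below, and the largest averages about 3.
- Chi-square rejects at 0.05 in 5.3% of trials; one-way ANOVA rejects in 89.1%.

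Under a real difference of 7 points, the literal test therefore rejects no more often than its nominal error rate.

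The article gives no SDs for PES, so no power was computed. Each subscale has 31 possible values. If all occurred, the average expected count would be 50 / 31 ≈ 1.6, which is also sparse.

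**4. ANOVA on a binary delivery outcome**

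Illustration with cesareans in 27, 15 and 15 of 50, so 57 of 150 = 0.38 overall. Expected counts are 19 and 31 in each group.

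- Chi-square = 64/19 + 2 × 16/19 + 64/31 + 2 × 16/31 = 8.15 on 2 degrees of freedom, p = 0.0170.
- ANOVA on 0/1 data: between-group sum of squares = 50 × (0.16² + 2 × 0.08²) = 1.92; within-group sum of squares = 50 × (0.54 × 0.46 + 2 × 0.30 × 0.70) = 33.42. F = (1.92/2) / (33.42/147) = 4.22 on 2 and 147 degrees of freedom, p = 0.0165.

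The two nearly coincide. ANOVA loses its meaning only for an unordered outcome with more than two categories, and the article does not say whether birth preference is one.

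**The case against.** The strongest reply is that this is a slip that nobody would act on. Chi-square and one-way ANOVA are the right pair of tests for three groups, and only the order of two words is wrong. The Sample size section shows the intended assignment, and the paired t test in the same paragraph presupposes continuous scores. An analyst who sized fear of childbirth as a mean difference is unlikely to cross-tabulate raw totals, so the sparse-table result describes something improbable.

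Much of this stands. It is very probably a word-order slip, and the realistic harm is a written rule that cannot be carried out sensibly as it reads. But the Sample size section only implies the right assignment; nothing in the article corrects the sentence. A prespecified rule should be usable as written, so that the eventual analysis need not be explained as a departure from it.

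A reader might go further and infer that the stated test is wrong for every outcome in the trial. The article does not support that: the feasibility outcomes have no test, and the paired t test suits the scores. A reader might also infer that the analysis of type of delivery would be badly distorted. Step 4 shows otherwise for two categories.

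**Conclusion.** The error is in the current text, and it contradicts the Sample size section. Its scope is the between-group comparison of the four secondary outcomes.

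The harm is uneven. If the sentence were followed, it would be severe for WDEQ-A and is expected to be similar in kind for the PES subscales. It is negligible for a two-category delivery outcome and undetermined for birth preference. The 5% and 89% figures depend on the assumed means, normality and a common SD in the study groups; the finding of reversal depends on no number.

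The sentence should be corrected, but it casts no doubt on the feasibility decision and changes no sample size. The printed n of 50 for type of delivery does not follow from the numbers in its formula, which give about 59. That is a separate matter and plays no part here.

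**What to change.** Swap the two terms in the Analytic plan so that chi-square is named for the qualitative variables (birth preference and type of delivery) and one-way ANOVA for the quantitative variables (the two PES subscales and WDEQ-A). Naming the outcomes beside each test would remove any doubt. The cost is one sentence, with no change to data collection or sample size.

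An optional improvement, separate from the error, is to compare the 36–38 week PES and WDEQ-A scores by ANCOVA, adjusting for the 18–20 week scores already collected.

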# Comparing the effect of in-person and virtual childbirth preparation trainings on the fear of childbirth (FOC) and pregnancy experience of pregnant women: protocol for a quasi-experimental feasibility study

**DOI:** 10.1186/s40814-021-00933-w

**Published:** 2021-11-05

**Keywords:** Childbirth preparation, Fear of childbirth, Pregnancy experience, Type of delivery, Virtual education, Feasibility study

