## Abstract

**Background:**

Childbirth preparation trainings are an important component of prenatal education, and pregnant women are increasingly interested in seeking information from online sources. The aim of this study is to compare the feasibility and the effects of in-person and virtual childbirth preparation training courses on the pregnancy experience, fear of childbirth (FOC), birth preference, and type of delivery among pregnant women.

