The primary objective of study is the feasibility of recruitment and feasibility of intervention adherence of participants in both in-person and virtual education groups. The secondary objectives are the effect of childbirth preparation training courses using two in-person and virtual education methods on the pregnancy experience, FOC, birth preference, and type of delivery in pregnant women.

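### The stated between-group tests are three-group omnibus tests, which alone answer neither the virtual vs in-person question nor the training vs control contrasts used for sizing

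*Protocol article*

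**What the plan says.** Three parts of the protocol article point at three different comparisons.

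- **Title and aim: virtual vs in-person.** The title opens "Comparing the effect of in-person and virtual childbirth preparation trainings on the fear of childbirth (FOC", and the abstract's Background states: "The aim of this study is to compare the feasibility and the effects of in-person and virtual childbirth preparation training courses". The end of the Introduction is broader. It makes feasibility primary and continues: "The secondary objectives are the effect of childbirth preparation training courses using two in-person and virtual education methods".
- **Sample size: training vs control.** The main calculation uses "a test power of 80% and a significance level of 0.05" and assumes that both forms of education act on type of delivery, "leading to a 25% decrease in cesarean sections, compared to the control group". The formula compares 0.55 with 0.30. The fear-of-childbirth calculation is also a two-group formula, intervention vs control, with a difference of 7 and SDs of 13.1 and 9.7.
- **Analytic plan: all three groups at once.** Here "the Chi-square test and one-way analysis of variance (ANOVA) will be used to compare the quantitative and qualitative variables in three groups". For change within a group, the paired t "test will be employed for intragroup comparison". The threshold is p<0.05. No pairwise contrast, follow-up procedure or interval is named.

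**The concern.** An omnibus test rejects when any group departs from the others. A significant result therefore does not say whether the two formats differ, whether both differ from control, or whether only one does. Followed as written, the plan produces no virtual vs in-person result and no training vs control result.

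A significant result is the one that needs care. The planning assumption gives both formats the same benefit, so in the protocol's own scenario the three-group test is likely to be significant while the formats are identical. A reader of a paper with this title could take such a p value as a difference between formats.

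The source of the controls adds to this. The Setting section draws them from women who do not want to deliver at this hospital or attend the classes, whereas both training groups come from women who do. The control group could therefore differ through selection, and that too could make the omnibus test significant without any difference between formats.

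**Working it through.** **Inputs (Sample size section).** Cesarean 0.55 in control and 0.30 with training; two-sided 0.05; 55 per group, or 50 before the 10% allowance for loss. WDEQ-A difference 7; SD 13.1 intervention, 9.7 control. Chi-square is taken for type of delivery and ANOVA for WDEQ-A. The sentence in the plan pairs tests and variable types the other way round, but that is a separate matter and does not affect this point.

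**The plan's own figures.** Both sizing formulas are two-group formulas.
- Fear: (1.96+0.84)² × (9.7²+13.1²)/7² = 7.84 × 265.7/49 = 42.5, so the stated 43 reproduces.
- Cesarean, with the printed inputs: [1.96·√(2×0.42×0.57) + 0.84·√(0.55×0.45+0.3×0.7)]²/0.25² = 59.3, not the stated 50. That is a separate error. I use 50 per group below because it is the protocol's number of completers.

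**Scenario 1: both formats work equally (the planning assumption).** Cesarean virtual/in-person/control = 0.30/0.30/0.55.
- Mean proportion = 1.15/3 = 0.3833.
- Sum of squared deviations = 2(0.0833)² + (0.1667)² = 0.0417.
- Noncentrality = 50 × 0.0417/(0.3833×0.6167) = 8.81. On 2 df this gives about 76% power.
- Simulation (100,000 trials): the three-group chi-square rejects in 76.6%. A direct virtual vs in-person test rejects in 4.9%.
- Among the omnibus rejections, the virtual vs in-person pair is significant in 6.2%, so about 94% come without a significant format difference.
- At 55 per group: 80.3% rejection, again 94%.

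**Scenario 2: only in-person works.** 0.55/0.30/0.55.
- Mean = 1.40/3 = 0.4667. The sum of squared deviations is again 0.0417.
- Noncentrality = 50 × 0.0417/(0.4667×0.5333) = 8.37, about 74% power.
- Simulation: 75%.

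The two scenarios have opposite implications for the title question and nearly the same omnibus rejection rate.

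**WDEQ-A**, SD 13.1/13.1/9.7, 50 per group.
- Means −7/−7/0: ANOVA rejects in 88%, a direct virtual vs in-person t test in 5%. About 94.5% of the rejections come without a significant format difference.
- Means 0/−7/0: ANOVA rejects in 84%.

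**Size of the tests.** With all three groups equal, both the chi-square and the ANOVA reject in about 5%.

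**Sensitivity for cesarean (assumed values; the protocol gives no virtual vs in-person difference).** Share of significant omnibus results in which only contrasts with control are significant:

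| Virtual/in-person/control | Control contrasts only |
|---|---|
| 0.30/0.30/0.55 | 94% |
| 0.35/0.30/0.55 | 88% |
| 0.40/0.30/0.55 | 73% |
| 0.30/0.425/0.55 | 62% |
| 0.30/0.425/0.425 | 27% |
| 0.30/0.55/0.55 | 11% |

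**Precision of the missing contrast, 50 per group.** Cesarean near 0.30: 1.96·√(2×0.3×0.7/50) = 0.18. WDEQ-A: 1.96·SD·√(2/50) = 4.5 for SD 11.5 (the root mean square of 13.1 and 9.7) and 5.1 for SD 13.1. Power of the direct test against 0.30 is 8% for 0.35, 18% for 0.40 and 34% for 0.45.

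**The case against.** The strongest objection is that the article is a condensed account. Follow-up tests after an ANOVA are routine, a full protocol or SAP may name them, and naming an omnibus test does not exclude them. As far as the choice of post hoc method goes, that stands. It does not remove the mismatch in the text itself: the aim is one pair, the sample size is another kind of pair, and the stated test is neither.

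It can also be said that no sentence commits the authors to reading an omnibus p value as a format difference, and that the planned descriptive tables would show 30/30/55 and 55/30/55 to be different patterns. Both are true. The limitation is of the omnibus p value alone, and group frequencies by themselves carry no inference about a pair.

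Two stronger readings are tempting and should not be drawn:
- **Inflated type I error.** A reader might compare 77% or 88% with the nominal 5%. Those rates are ordinary power: the control group does differ in that scenario, so the three-group null is false. When all groups are equal the rate is 5%.
- **A significant result usually reflects the control group alone.** That holds only if both formats work about equally well. If one format is inert, the share falls to about 11%. Equal benefit is the protocol's planning assumption, and its Introduction calls the evidence on these trainings conflicting.

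Finally, the effect outcomes are secondary. The feasibility criteria have their own thresholds, which these tests do not touch. That limits the stakes.

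**Conclusion.** The point holds as a mismatch between question and test. The stated between-group tests, taken alone, give no answer on virtual vs in-person or on either training vs control contrast. Under the protocol's planning values at 50 per group, the three-group chi-square on cesarean is significant in about 77% of trials when the formats are identical and about 75% when only one works. In the first case, about 94% of the significant results come without a significant virtual vs in-person difference.

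These figures rest on the assumed 0.55 and 0.30, independent observations and 50 completers per group. They do not show that the omnibus test is invalid. The matter concerns secondary outcomes and is worth correcting because the correction is nearly free.

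**What to change.** In the Analytic plan, add three prespecified pairwise contrasts for each effect outcome: virtual minus in-person, virtual minus control, and in-person minus control. Report each as a difference with a 95% CI: a difference in proportions for type of delivery and birth preference, and a difference in means for WDEQ-A and each PES subscale.

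For multiplicity, either keep the omnibus test as a gate and test pairs at 0.05 only after it rejects (with exactly three groups this holds the familywise rate at about 5%), or use Holm. With the gate, the virtual vs in-person test still rejects in about 5% of trials under 0.30/0.30/0.55. State that a significant omnibus result alone supports no statement about virtual vs in-person.

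The cost is a few lines of text and three contrasts per outcome, with no extra data or participants. The drawback is visible imprecision: about ±18 percentage points for cesarean and ±4.5 to 5 points on WDEQ-A. With power of 8% to 34% for assumed cesarean differences of 5 to 15 points, the virtual vs in-person result should be presented as an estimate with its interval, not as a settled comparison.

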## Methods

### Setting

The required data will be collected from childbirth preparation training courses that are regularly held in Milad Hospital, Tehran, Iran. These courses have high educational quality and are based on a precise schedule, according to the educational plans defined by the Ministry of Health and Medical Education of Iran. Notably, these courses are held in classes that contain 10-12 individuals at the prenatal clinic of Milad Hospital, which is one of the main referral hospitals in Tehran province.

At Milad Hospital, where all participants in the three groups will be selected from, it is mandatory for pregnant women to attend childbirth preparation classes in order to deliver their children at this hospital, so women who wish to give birth in this hospital have to participate regularly in these classes (participating in six sessions from eight at least). The samples in the virtual and in-person intervention groups will be selected among these women. There is another group of women who only visit a specialist or midwife to receive a pregnancy care and advice, and do not want to give birth at Milad Hospital or attend the preparation classes. These people will be used for the control group.

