### Research design and sampling

This feasibility quasi-experimental study with a control group was reported in accordance with the Consolidation Standards of Reporting Trials (CONSORT) statement for pilot and feasibility trials (Additional file 1) [17]. The current study will be conducted on 165 primiparous women with 18-20 gestational weeks that will be selected by convenience sampling method. The researcher will attend the prenatal clinic for sampling on a daily basis. The participants will be equally allocated into two studies and one control groups (Fig. 1). The participants in study groups A and B will receive virtual and in-person childbirth preparation trainings, respectively. Also, the control group will receive no education on childbirth preparation during pregnancy.

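### Three non-randomised groups are compared with no adjustment for the PES, WDEQ-A and demographic data already collected at baseline

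*Protocol article*

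**What the plan says.** All from the protocol article.

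- **How groups arise.** Under Research design and sampling, the women "will be selected by convenience sampling method" and "The participants will be equally allocated into two studies and one control groups". The study is quasi-experimental and no randomisation is described. Under Setting, both trained groups come from women who want to deliver at the hospital and must attend classes. Other women "do not want to give birth at Milad Hospital or attend the preparation classes", and "These people will be used for the control group".
- **What is measured.** Under Measurements and feasibility outcomes, the first time point is "Recruitment (demographic characteristics questionnaire, PES, WDEQ-A" at about 18-20 weeks, and the second is "36-38 weeks (PES, WDEQ-A, and birth preference) (T2". Under Data collection, the demographic form includes age, education and economic status.
- **How it is analysed.** Under Analytic plan, besides chi-square, "one-way analysis of variance (ANOVA) will be used to compare the quantitative and qualitative variables in three groups". I read this as ANOVA for scores and chi-square for categories, although the sentence's word order pairs them the other way. A paired *t* "test will be employed for intragroup comparison", and p below 0.05 counts as significant. No covariate, matching or regression is named, and the quantity entered into the ANOVA (second score or change) is not stated.

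**The concern.** Trained and control women are separated by their own choice of hospital and classes, so equal starting levels of fear, pregnancy experience or social background cannot be assumed. One-way ANOVA and chi-square take no covariates, so a difference present at baseline can appear as a training effect.

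The paired tests do not help. The Introduction itself expects anxiety and stress to rise as the due date approaches, so a change from 18-20 to 36-38 weeks mixes that drift with any effect of training.

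Chi-square on type of delivery has a related weakness. The Discussion names fear of vaginal delivery as the leading reason for caesarean section, which makes baseline WDEQ-A prognostic on the protocol's own reasoning, yet it is not used.

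At stake are the estimates for FOC, PES, birth preference and type of delivery. These are secondary objectives, but they carry sample size calculations and significance tests, and the Discussion presents effects on experience, fear and vaginal delivery among the main results.

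**Working it through.** **Inputs from the protocol (Sample size).** WDEQ-A SDs 13.1 and 9.7; target difference 7 points; two-sided 5% level (1.96); 80% power (0.84); 55 per group with 10% loss, so about 50 evaluable.

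**Assumed, because the protocol gives no figure.** Baseline gap between two groups of 2 to 5 WDEQ-A points; correlation r between the T1 and T2 scores of 0.3 to 0.7.

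**Step 1: the protocol's own figure.** n = (1.96 + 0.84)² × (9.7² + 13.1²) / 7² = 7.84 × 265.7 / 49 = 42.5, so 43 per group. This reproduces. The formula has no baseline term.

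**Step 2: ANOVA on T2 scores.** The SE of a pairwise difference is √(265.7/50) = 2.31. With no training effect and equal spread at T1 and T2, a baseline gap g leaves r × g at T2. The false-positive rate is P(|Z + r·g/2.31| > 1.96):

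| Baseline gap | r = 0.3 | r = 0.5 | r = 0.7 |
|---|---|---|---|
| 2 points | 6% | 7% | 9% |
| 3.5 points | 7% | 12% | 19% |
| 5 points | 10% | 19% | 33% |

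At the last cell 0.7 × 5 = 3.5 points remain, half the target difference of 7.

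**Step 3: other analyses and another gap model.** A three-group simulation used 50 per group, 5,000 runs, no effect, and one group shifted at baseline by 0.3 SD. That is about 3.5 points, since the root-mean-square SD is √(265.7/2) = 11.53. Rejection rates over r = 0.3 to 0.7:

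| Analysis | Gap shrinks to r × g | Gap persists in full |
|---|---|---|
| ANOVA on T2 | 7%-18% | 31%-32% |
| ANOVA on change | 8%-14% | 5% |
| ANCOVA | 5% | 10%-18% |

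Change scores are sound if the gap persists and biased if it regresses. ANCOVA is the reverse. No method is right under both.

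**Step 4: paired tests.** Suppose all three groups drift by the same 0.2 SD with no group effect, and r = 0.5. Each paired test is then significant 28% of the time. The chance that the three do not all agree is 1 − 0.284³ − 0.716³ = 61%.

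**Step 5: precision.** Relative to T2-only analysis, ANCOVA multiplies the variance by 1 − r² and change scores by 2(1 − r):

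| r | ANCOVA factor | 50 women worth | Change-score factor |
|---|---|---|---|
| 0.3 | 0.91 | 50/0.91 = 55 | 1.4 |
| 0.5 | 0.75 | 50/0.75 = 67 | 1.0 |
| 0.7 | 0.51 | 50/0.51 = 98 | 0.6 |

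The ANCOVA factor is slightly optimistic when groups differ at baseline. Unadjusted power for 7 points at 50 per group is already about 86%.

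**The case against.** - **The analysed quantity is open.** If the ANOVA is on changes, the raw gap is subtracted and the table in Step 2 does not apply. This stands, so the 6% to 33% is conditional. It does not clear the plan: change scores keep regression to the mean, are less precise than ANCOVA at any r below 1, and leave demographics unadjusted.
- **Self-selection covers only part of the design.** A reader might infer that women also choose between virtual and in-person training. The protocol does not say so: both trained groups come from the same class-attending women, and how they are divided is not described. The documented selection is training versus control.
- **The paired tests are an addition.** A reader might infer that the plan will claim a difference because one group's paired test is significant and another's is not. It does not say that. The 61% shows only why such a reading should be ruled out.
- **The top of the range is an unfavourable corner.** The 33% needs a 5-point gap and r = 0.7. The article reports a Persian WDEQ-A alpha of 0.64. Alpha is not a strict ceiling, but if it approximates reliability, r = 0.7 looks high. The whole range should be read.
- **ANCOVA is not a cure.** It still rejects 10% to 18% of the time when a 0.3 SD gap persists, and an imperfectly reliable baseline score under-corrects. This stands and shapes the fix.
- **Covariates are often left to a fuller document.** True, and an article that was merely silent would not be faulted. Here the tests are named, and they take no covariates.

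**Conclusion.** The point holds for the training-versus-control comparison. The plan names unadjusted tests for groups separated by the women's own choice, while holding baseline scores and demographics that it does not use. If T2 scores are compared, the pairwise false-positive rate for WDEQ-A is about 6% to 33%. That rests on an assumed gap of 2 to 5 points, an assumed correlation of 0.3 to 0.7, and a gap that shrinks in proportion to that correlation. If changes are compared, the raw gap goes but regression to the mean stays.

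Bias is the main issue. The precision gain, 50 women worth about 55 to 98, is a secondary benefit. A reader might infer that the WDEQ-A comparison is underpowered without adjustment; at about 86% power for the stated difference, it is not. Nor are the recruitment and adherence criteria, the primary outcome, touched. This should be changed before analysis, but it does not threaten the feasibility question.

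**What to change.** In the Analytic plan:

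1. State that the between-group analysis of T2 WDEQ-A and of each PES subscale is ANCOVA with group, the T1 value of the same scale, age, education and economic status.
2. Analyse type of delivery by logistic regression, and birth preference by logistic or multinomial regression according to its categories (the article does not say that it is binary). Use group, T1 WDEQ-A and the same demographics. Neither outcome has a baseline value of its own.
3. Report adjusted group differences (odds ratios for the categorical outcomes) with 95% confidence intervals.
4. Keep paired changes as description, with no claim of effect from their p-values.
5. State that adjustment reduces but does not remove selection bias. In particular, control women do not plan to deliver at this hospital, so group is tied to place of delivery, and the listed covariates cannot correct for that.

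The cost is analysis wording only. Every covariate is already collected, the models are standard in SPSS, and no extra women, visits or questionnaires are needed.
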